### Study protocol

After written informed consent is obtained patients are enrolled in the study and baseline data are documented (visit 1). Subsequently, patient’s medical treatment data are recorded throughout the regular treatment. No additional examinations or interventions are carried out by reasons of the study. At discharge medical treatment data are documented in the case-report-form (visit 2). One year after symptom onset patients or their legal representatives are contacted by phone or letter (visit 3). Follow-up data are also documented in the CRF. After completion a copy of the CRF and a compact disc containing the patients’ pseudonymized neuroimaging data is sent to the coordinating center (Center for Stroke Research Berlin (CSB)), which is responsible for data management and analysis.

### Data collection

Baseline documentation of clinical data includes demographic factors, past medical history, history of present illness, and the previous functional status measured on the mRS and NIHSS. Imaging data includes infarct localization, presence of space-occupying edema, and hemorrhagic transformation. Considering conservative treatment measures, the use of ICP-lowering drugs, and data on sedation, muscle relaxation and mechanical ventilation will be recorded. With respect to surgical procedures, the time-to-surgery, the diameter of craniotomy, and the type of duraplasty will be recorded. Complications during the initial hospital stay will also be recorded. At follow-up, data acquisition is done using a structured interview including the modified Rankin Scale, the Barthel-Index, the EuroQoL-5D, the SF-36, and the Hamilton Depression Rating Scale (HDRS). Furthermore, complications during the follow-up period and, if applicable, the retrospective consent to treatment will be recorded.

### Outcome measures

The primary outcome measure is functional outcome as determined by the mRS score, dichotomized between 0–4 and 5 or 6 at 1 year ± 14 days after symptom onset in the subgroup of patients additionally fulfilling the inclusion criteria of the RCT. Secondary outcome measures are: (a) mortality, (b) median time of survival assessed by the Kaplan-Meier estimator, (c) functional outcome as determined by the mRS Score dichotomized between 0–3 and 4–6 at 1 year ± 14 days after symptom onset, (d) treatment modes (i.e. osmotherapy, hyperventilation, sedation, etc.), assessed at discharge if applicable, time to decompressive surgery, diameter of bone flap/craniectomy measured in situ and by neuroimaging, type of duraplasty, if applicable, as well as complications (i.e. hygroma, impaired wound healing, epidural and subdural hematoma, parenchymatous hematoma, wound and bone flap infections) and (f) time to cranioplasty assessed 1 year ± 14 days after symptom onset if applicable, other complications (i.e. pneumonia, and any other infection, thrombosis, seizures), (g) quality of life determinded by the SF-36 and EuroQoL-5D questionnaires and depression assessed by the HDRS, and (h) rate of retrospective consent to treatment assessed 1 year ± 14 days after symptom onset.

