**Methods/Design:**

DESTINY-R is a prospective, multicenter, open, controlled registry including a 12 months follow-up. The only inclusion criteria is unilateral ischemic MCA stroke affecting more than 50% of the MCA-territory. The primary study hypothesis is to confirm the results of the RCT (76% mRS ≤ 4 after 12 months) in the subgroup of patients additionally fulfilling the inclusion cirteria of the RCT in daily routine. Assuming a calculated proportion of 0.76 for successes and a sample size of 300 for this subgroup, the width of the 95% CI, calculated using Wilson's method, will be 0.096 with the lower bound 0.709 and the upper bound 0.805.

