[13]. Indeed, some authors and the latest meta-analysis defined favorable as a mRS of ≤ 3
[4]. Other authors think that the question of favorable (or in such severe diseases rather “acceptable”) outcome should be answered by the patients themselves. Unfortunately, the contradictory data on quality of life and retrospective consent to hemicraniectomy after malignant MCA infarction that are currently found in the literature are of little help in preoperative decision making
[5,9,14-18]. Fourth, the actual effectiveness of conservative treatment has never been addressed in detail, e.g. the RCT showed different outcomes in the conservative treatment groups: patients who were treated on an intensive care unit
[5] had a higher rate of survival (47% vs. 22%) and more often better functional outcome (mRS 0–4: 33% vs. 0%) than patients treated on a stroke unit or a general ward
[6]. Fifth, despite the life-saving character of DHC, the overall case fatality rate in patients who underwent surgery in the RCT was still 29%
[7]. This means that nearly every third patient dies for reasons not well understood. Similarly, no valid data are available on the actual rate of complications especially concerning re-implantation of the skull.

Most of these issues are a commonplace in the scientific community and have been addressed in a number of case series and non-randomized case control studies
[19-21]. However, most of these studies are retrospective in nature, lack appropriate control groups, and show heterogeneous or inconclusive results. Therefore, proper investigation in a large-size, prospective study is urgently needed. Besides, the implementation of hemicraniectomy in clinical practice has not been reviewed since the publication of the RCT.

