### Sample size calculation

Assuming a calculated proportion of 0.76 for successes in the subgroup of patients additionally fulfilling the inclusion cirteria of the RCT, and a sample size of 300 for this subgroup, the width of the 95% CI, calculated using Wilson's method, will be 0.096 with the lower bound 0.709 and the upper bound 0.805
[22]. Given an estimated enrolement of 4 patients per center/year at 45 study centers plus one year of follow-up, data acquisition would be concluded in 3 years. Thus the end of the study is planned for 2014.

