## Discussion

We advocate the use of a prospective register to further characterize patients with malignant MCA infarction and evaluate implementation, effectiveness and adverse events of current treatment concepts, including DHC. Although first trends in prevalence and outcome of DHC are promising and seem comparable to the results of the RCT
[23,24], the use of a large database allows the representation of a much broader population of patients treated for malignant MCA infarction. The anticipated sample size should allow confirming the results of the RCT and raising new hypotheses even if the population turns out to be more heterogeneous than expected. The planned inclusion of at least 300 patients in a reasonable time frame can only be achieved in a multicenter approach. The open design allows continuing initiation of cooperative study centers. The very conservative estimate of 4 patients/year per center would probably allow extending patient recruitment to 500 or even 1000 if certain questions would need a larger sample size to be investigated. However, due to the nature of a prospective registry, only hypotheses may be created, which then need further investigation in RCT.

To avoid the investigation of a very restricted group of patients, the inclusion criterion of infarct size was intentionally set comparatively wide. Thus any patient with a MCA infarction involving more than 50% of the territory can be included irrespective of treatment, although eligibility criteria for the RCT were infarction of more than 2/3 of the MCA territory. However, as the individual factors promoting infarct swelling are not well understood yet, not considering these patients may possibly exclude a subgroup of patients that would have the potential to benefit from a certain treatment option in the future. The limited number of eligibility criteria are easy to implement even in small hospitals with limited staff and will most likely result in a patient mix representative of clinical practice. Conservatively treated patients are followed simultaneously and constitute the control group, which may be compared to surgically treated patients in this parallel design. Due to treatment bias it may be possible that treatment groups show significantly different baseline data making a true comparison difficult. The expected number of patients should, however, be large enough to compensate for lower event rates or differences in baseline data.

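### The primary analysis set has no treatment condition, but its 76% benchmark cannot describe operated and conservatively treated patients together

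*Protocol article*

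**What the plan says.** The Abstract (Methods/Design) states the aim: "The primary study hypothesis is to confirm the results of the RCT (76% mRS ≤ 4 after 12 months"), in registry patients who also meet the trials' inclusion criteria. Outcome measures defines the primary outcome as mRS 0–4 versus 5–6 at one year "in the subgroup of patients additionally fulfilling the inclusion criteria of the RCT". Sample size calculation uses the same set and gives it the same figure: "Assuming a calculated proportion of 0.76 for successes in the subgroup of patients additionally fulfilling" the RCT criteria, with "a sample size of 300 for this subgroup". The resulting 95% Wilson interval has a width that "will be 0.096 with the lower bound 0.709 and the upper bound 0.805". None of the three places makes hemicraniectomy a condition of membership, and none says which arm of the trials the 76% comes from.

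Study design says that the registry does not allocate treatment. The Discussion says that patients enter whatever their treatment, and adds: "Conservatively treated patients are followed simultaneously and constitute the control group".

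**The concern.** Inclusion criteria of a randomised trial are met before treatment is assigned, so meeting them does not separate operated from conservative patients. Read literally, eligible conservative patients count in both the numerator and the denominator of the primary proportion. That proportion is then compared with 76%, which also serves as its expected value for planning.

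If 76% belongs to operated patients only, the primary estimate depends on how often the participating centres operate as well as on how operated patients fare. A registry whose operated patients reproduced the trials exactly could then appear not to confirm them.

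**Working it through.** **Inputs**
- Benchmark and planning value 0.76, n=300 (Abstract; Sample size calculation).
- Treatment mix in the randomised evidence: 58 operated, 51 conservative, 109 in all (Background, from the latest meta-analysis).
- mRS 0–4 in conservative patients: 33% in one trial and 0% in another; survival there 47% and 22% (Background, two of the three trials).
- Case fatality in operated trial patients: 29% (Background, from the pooled analysis).
- Share of RCT-eligible registry patients treated conservatively: not given. Values of 10–30% below are assumptions.

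**1. The plan's own interval.** With z=1.96, the Wilson centre is (p + z²/2n)/(1 + z²/n) and the half-width is z·√[p(1−p)/n + z²/4n²]/(1 + z²/n). For p=0.76 and n=300 these are 0.7567 and 0.0481, giving 0.709 to 0.805 and width 0.096. The stated figures are reproduced.

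**2. Can 76% be an all-patient result?** Suppose every operated patient succeeded:
- conservative success 0%: 58/109 = 0.532
- conservative success 33%: (58 + 0.33×51)/109 = 74.83/109 = 0.687

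Both are below 0.76. Reaching it would need (0.76×109 − 58)/51 = 24.84/51 = 0.487 success in conservative patients. That exceeds both quoted success rates, and even the better of the two survival rates (47%).

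It is not a conservative-arm result either, since those rates are 0–33%. The operated arm is what remains.

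**3. Does 76% fit the operated arm?** Not with the figures quoted. If 29% of operated patients died by 12 months, at most 1 − 0.29 = 0.71 can have mRS 0–4. This does not bring back the mixed reading: with operated success at 0.71, an overall 76% would need (0.76×109 − 0.71×58)/51 = 41.66/51 = 0.817 in conservative patients.

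**4. Effect of pooling.** Let s be the conservative share, 0.76 the operated success and c the conservative success. The pooled proportion is (1−s)×0.76 + s×c.

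| Assumed s | c = 0% | c = 33% |
|---|---|---|
| 10% | 0.684 | 0.717 |
| 20% | 0.608 | 0.674 |
| 30% | 0.532 | 0.631 |

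At s=20% and c=33%, the expected Wilson interval at n=300 is 0.619 to 0.725.

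At n=300 the upper Wilson limit falls below 0.76 once the proportion is below about 0.7117. That corresponds to s = (0.76 − 0.7117)/0.76 ≈ 6.4% for c=0%, and s = (0.76 − 0.7117)/(0.76 − 0.33) ≈ 11.2% for c=33%.

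**5. Precision in an operated-only set.** If 300 operated patients are analysed, the stated interval stands. If 300 is the total number eligible, the operated set is smaller:

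| Operated n | Wilson interval at 0.76 | Width |
|---|---|---|
| 240 (s=20%) | 0.702–0.810 | 0.108 |
| 210 (s=30%) | 0.698–0.813 | 0.115 |
| 150 (s=50%) | 0.686–0.821 | 0.136 |

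**The case against.** The strongest reply is that operated patients are plainly meant. The Abstract frames the question around early hemicraniectomy, the Discussion treats conservative patients as a comparison group, and Data analysis plans group comparisons. The article is also a condensation, and the full protocol may define the set more closely. What stands is that pooling is the literal reading and not a declared intention. It does not remove the point: the article itself fixes the primary population, benchmark and planning value, the population is worded without a treatment condition in all three places, and the general group comparisons do not redefine it.

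A second reply is that the analysis is descriptive, with no test or decision rule, and that the data can still be split by treatment. That is correct, and no data are lost. The declared aim is nevertheless to confirm a specific figure, and a descriptive proportion set against a benchmark for another population misleads in the same way.

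A third reply concerns the size of the effect. The 0% rate comes from patients on stroke units or general wards, whereas all registry centres have intensive-care experience. With 33% success and a 10% share the pooled value is 0.717, inside the planned interval. This stands, and is why only a range can be given.

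A reader might also infer that the subgroup cannot be derived because infarct extent above two thirds of the territory is not listed among the recorded items. The article does not support that: all imaging goes to the coordinating centre, where extent could be read, and Data collection is only a summary of the form.

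**Conclusion.** The concern holds. The primary set and its benchmark do not match as written, and the article's own counts and rates show that 76% cannot be a result for both treatments combined. Under operated success of 76% and conservative success of 0–33%, assumed shares of 10, 20 and 30% lower the pooled proportion to 0.68–0.72, 0.61–0.67 and 0.53–0.63.

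Three stronger conclusions may tempt a reader and are not supported:
- **That 76% is established as the operated-arm result.** The arm is inferred by elimination, from conservative rates in two of three trials and counts from a different source, and the 29% case fatality contradicts it. The time point of that 29% is not stated, so the two figures have to be reconciled at source.
- **That a downward bias of known size is certain.** The conservative share is not given. The direction rests on eligible conservative patients doing worse than operated ones, as in the trials. The Discussion itself warns of treatment bias, and selection of milder cases for conservative care could reduce the effect.
- **That restricting the set guarantees agreement with 76%.** If operated success were 0.71, the Wilson interval at n=300 would be 0.656 to 0.758, which still excludes 0.76. The restriction makes the comparison like with like; it does not settle the benchmark.

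**What to change.** 1. In the Abstract, Outcome measures and Sample size calculation, define the primary set as patients who meet the RCT inclusion criteria and underwent hemicraniectomy. If a surgery time window applies, take it from the trials' criteria and state it; the article says only that benefit was found within 48 hours.
2. Name the source and arm of the 76% and reconcile it with the 29% operated case fatality.
3. Tie n=300 and its interval to this set. If 300 is the total eligible number, restate the precision (width 0.108 at n=240, 0.136 at n=150). The Discussion's planned inclusion of at least 300 patients leaves open which is meant.
4. Report RCT-eligible conservative patients separately, against the trials' conservative result.

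**Cost.** The change is to the text, but the set becomes smaller and its interval wider, or recruitment takes longer. At 4 patients per centre per year in 45 centres, two years of enrolment before the follow-up year gives 4×45×2 = 360 registry patients, which leaves little room for 300 who are both eligible and operated. Conditioning on surgery also leaves out patients who die before it, which can favour the registry over a randomised surgical arm. The report should acknowledge this.

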## Background

Severe space-occupying middle cerebral artery infarction (malignant MCA infarction) is a worst case scenario in stroke medicine. Comparable to other devastating subtypes of stroke such as severe intracranial hemorrhage and basilar artery thrombosis therapeutic options are limited and questionable with respect to improved outcome. Even under maximum intensive care treatment most patients die after only few days due to relentless edema formation, brain tissue shift and transtentorial herniation
[1-3]. In contrast, decompressive hemicraniectomy (DHC) has been proven a life saving surgical intervention. Its efficacy in malignant MCA infarction has been demonstrated in three randomized controlled trials (RCT), their a pooled-analysis, and a recent meta-analysis: Early DHC within 48 hours significantly reduces mortality and improves the chance of surviving with mild to moderate disability without increasing the risk of most severe disability
[4-7].

Although the RCT and the two analyses gave answer to the most pertinent question, they were not powered for other important issues: First, due to the strict inclusion criteria of the RCT, only healthy and independent young patients (18–60 years) were treated. In addition, a positive treatment effect was only found within 48 hours after stroke onset
[4-7]. Therefore, it is unclear if the results can be extrapolated to real world situations, when co-morbidities and dependency are common and the decision to proceed with decompressive surgery is made later on in the course of the disease. Second, since the RCT were not powered for adequate subgroup analysis - only 109 patients were included in the latest meta-analysis, 58 underwent DHC and 51 were treated conservatively
[4]- it remains unclear which individual patients benefit from surgical decompression, e.g. with respect to age, presence of aphasia, and timing of surgical intervention. Moreover, it remains unclear which clinical or radiolgical factors sufficiently predict edema formation and thus allow selection of patients for DHC in advance of clinical deterioration
[8-12]. Third, with respect to the extent of the infarction and the unrealistic expectation of complete recovery after severe stroke, “favorable” outcome was defined as a score of ≤ 4 on the modified Rankin scale (mRS) in the pooled-analysis of the RCT
[7]. It is a matter of ongoing debate amongst experts if such a condition may be classified as “favorable”

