### Study subject recruitment

At each study site patients older than 18 years of age are screened and asked for participation if they meet the following inclusion criteria: (a) clinical signs of unilateral MCA infarction, (b) ischemic infarction affecting at least 50% of the MCA territory confirmed by computed tomography (CT) or magnetic resonance imaging (MRI). Additional involvement of the anterior and/or posterior cerebral artery territories may be present, (c) written informed consent of the patient or their legal representative. Because treatment is independent from participation in DESTINY-R there is no time interval for inclusion. The only exclusion criterion is a simultaneous or contemporary acute brain injury, e.g. traumatic brain injury or concomitant infarction contralateral or infratentorial in addition to the index- infarction.

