### Data analysis

All outcome measures will undergo descriptive data analysis, including mean, standard deviation, median, range, as well as absolute and relative frequencies depending on the scales of the variables. Additionally, descriptive *p*-values for group comparison and the corresponding 95% confidence interval will be indicated. Two-sample *t* testing, the Mann–Whitney *U*-test, or *χ*2-testing will be used to analyze group differences as applicable. Kaplan-Meier estimates and log-rank statistics will be used for assessing cumulative risk of death at 12 months. The comparability of different treatment groups will be depicted by comparing demographic and baseline data. Statistical analysis will be performed using the latest SAS software version (SAS Institute Inc., Cary, NC).

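### Secondary outcome (c), mRS 0–3 versus 4–6, ignores pre-stroke mRS although patients already at mRS 4–5 are admitted, so the all-patient rate and the unadjusted treatment comparison both depend on their share

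*Protocol article*

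**What the plan says.** All references are to the protocol article.

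- **Outcome measures.** Secondary outcome (c) is "functional outcome as determined by the mRS Score dichotomized between 0–3 and 4–6 at 1 year ± 14 days after symptom onset". The restriction "in the subgroup of patients additionally fulfilling the inclusion criteria of the RCT" is attached to the primary outcome (mRS 0–4 versus 5–6) and is not repeated for (c).
- **Study subject recruitment.** Adults with a unilateral MCA infarct of at least half the territory may enter, with consent. "The only exclusion criterion is a simultaneous or contemporary acute brain injury"; pre-stroke function is not limited.
- **Background.** In the randomised trials "only healthy and independent young patients (18–60 years) were treated". The article asks whether their results carry over to "real world situations, when co-morbidities and dependency are common".
- **Data collection.** Baseline documentation includes "the previous functional status measured on the mRS and NIHSS".
- **Data analysis.** "Two-sample *t* testing, the Mann–Whitney *U*-test, or *χ*2-testing will be used to analyze group differences as applicable". On baseline differences, "The comparability of different treatment groups will be depicted by comparing demographic and baseline data". The section names no adjusted analysis.
- **Discussion.** Conservatively treated patients are the control group. Treatment bias is acknowledged, but the expected number of patients is said to be large enough to make up for baseline differences.

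**The concern.** A fixed cut at mRS 3 is informative only for patients who could end on either side of it. A patient who lived at mRS 4 or 5 before the index infarct will be in the 4–6 category at one year under either treatment. The design admits such patients, and the Background describes dependency as common in the population of interest.

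Two readings of (c) are affected.

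1. **The overall proportion.** It falls as the share of previously dependent patients rises, even if treatment works exactly as well in everyone else. Set beside figures from independent trial patients, a lower value could be taken for lower effectiveness.
2. **Operated versus conservative patients.** Treatment is not allocated. If previously dependent patients are operated on less often, the cut alone produces a difference in favour of surgery. The named tests do not remove it, and a larger registry only makes it more likely to reach significance.

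**Working it through.** **The plan's own figure.** The only sample-size figure is the 95% Wilson interval for a proportion of 0.76 with n = 300. Recomputed, it runs from 0.7086 to 0.8048, width 0.0963, which agrees with the stated 0.709, 0.805 and 0.096. It concerns the primary outcome, not (c).

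**Population of (c).** No population is stated for (c). Two points favour the all-patient reading: the RCT restriction is attached only to the primary outcome, and the Discussion says the secondary outcomes allow subgroup analyses such as elderly patients, who lie outside the trials' 18–60 age range.

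**Inputs not in the documents (assumed).**
- f: share with pre-stroke mRS 4–5, taken as 2% to 20%.
- s: proportion reaching mRS 0–3 among the other patients, taken as 0.30 to 0.50.
- Patients with pre-stroke mRS 4–5 reach 0–3 with probability zero.

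**Overall rate.** Observed proportion = s(1−f), so the fall is s × f.

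| f | fall at s = 0.30 | fall at s = 0.50 |
|---|---|---|
| 2% | 0.6 points | 1.0 point |
| 5% | 1.5 | 2.5 |
| 10% | 3.0 | 5.0 |
| 20% | 6.0 | 10.0 |

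For example, with s = 0.40 the observed value is 0.38, 0.36 or 0.32 at f = 5%, 10% or 20%.

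**Treatment comparison with no treatment effect.** Operated minus conservative = s(1−f_operated) − s(1−f_conservative) = s × (f_conservative − f_operated).
- s = 0.40, f = 2% versus 15%: 0.40 × 0.13 = 0.052, or 5.2 points.
- Low end, s = 0.30, 2% versus 10%: 0.30 × 0.08 = 0.024.
- High end, s = 0.50, 2% versus 20%: 0.50 × 0.18 = 0.090.

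**Does sample size help?** This is the probability that the unadjusted two-sided 5% test favours surgery when there is no effect (nominal 2.5% in that direction), for s = 0.30 to 0.50. Equal groups are assumed: 150 each splits 300 evenly, and 500 each splits the 1000 that the Discussion mentions as a possible extension.

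| f operated vs conservative | difference | 150 per group | 500 per group |
|---|---|---|---|
| 0 vs 10% | 3–5 points | 8–14% | 18–35% |
| 0 vs 20% | 6–10 points | 21–41% | 57–89% |

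The shift stays the same as n grows, while the chance of a significant result rises.

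**After restriction to pre-stroke mRS 0–3.** Under the same assumptions both groups have expected proportion s, and the difference from this source is s − s = 0.

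**The case against.** The strongest case against has five parts.

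- **The confirmation of the trial results is not at stake.** A reader might infer that the comparison with the RCT is compromised. The documents do not support that. The confirmation uses mRS 0–4 versus 5–6 in patients meeting the RCT criteria, and the trial patients were independent. The article plans no RCT comparison for (c) and quotes no pooled mRS 0–3 proportion. This stands.
- **Misreading is not inevitable.** A reader might also infer that prior dependency will be taken for a treatment effect. The p-values are called descriptive, the Discussion says a registry can only generate hypotheses, and causal claims are disclaimed. This stands as a softening. The article nevertheless says it will inform on effectiveness, and its reassurance about sample size does not hold for bias.
- **The size is assumed.** This stands. Dependency being common does not say how many patients are at mRS 4–5. The only conservative-arm figures quoted are mRS 0–4 in 33% and 0%, and mRS 0–3 rates in those arms cannot be higher. With s = 0.33 the 5.2-point example becomes 0.33 × 0.13 = 4.3 points. The registry also admits smaller infarcts than the trials did, so s may be higher there. The direction of the treatment shift depends on which group holds more dependent patients, which the documents do not say.
- **The analysis plan could handle it.** Pre-stroke mRS is recorded and subgroup analyses are foreseen, so it could. The point, however, is about an outcome definition and tests that the article does state, and nothing shown corrects them.
- **The all-patient figure is legitimate, and restriction removes only one piece of confounding.** Both are right. The restricted figure therefore belongs beside the all-patient one, not in its place.

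**Conclusion.** The point holds for secondary outcome (c) only. As written, its all-patient proportion falls by s × f, and its unadjusted treatment comparison shifts by s × (f_conservative − f_operated) with no treatment effect. If f is about 2%, the overall rate moves by no more than about 1 point and the matter is minor. For f = 5–20% with s = 0.30–0.50 it moves by about 1.5–10 points.

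These sizes rest on assumed f and s and on a near-zero chance of reaching mRS 0–3 from pre-stroke mRS 4–5. The treatment shift also requires f to differ between the groups, which is plausible without allocation but not documented. The primary outcome is largely unaffected.

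**What to change.** Add to the definition of outcome (c), or to the analysis plan:

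1. Report the proportion with mRS 0–3 in all registered patients as a description of the registry.
2. Make the operated-versus-conservative comparison of (c), and any reading of (c) against RCT figures, in patients with pre-stroke mRS 0–3.
3. Report patients with pre-stroke mRS 4–5 separately, by survival and return to pre-stroke mRS.
4. Apply the same rule to any mRS 0–4 figure given outside the RCT-criteria subgroup, with pre-stroke mRS 0–4 as denominator.

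State alongside that this removes only the part of the bias due to patients who cannot succeed. Differences in age, comorbidity, infarct extent and pre-stroke mRS within 0–3 remain.

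The cost is a few lines of text and no new data, since pre-stroke mRS is already collected. The denominator of the comparison shrinks by the share f.

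### Time to cranioplasty is assigned ordinary descriptive statistics with no rule for patients who die first or are still waiting at one year, so the summary will tend to be too short, by an unknown amount

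*Protocol article*

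**What the plan says.** Outcome measures, item (f), makes the interval to skull re-implantation a secondary outcome: "time to cranioplasty assessed 1 year ± 14 days after symptom onset if applicable". The Study protocol section provides for one follow-up contact, a year after onset.

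Data analysis sets the method for every outcome: "All outcome measures will undergo descriptive data analysis, including mean, standard deviation, median, range, as well as absolute and relative frequencies", with the choice "depending on the scales of the variables". Group differences are tested by t, Mann–Whitney or chi-square tests as suits the variable, and the p-values are called descriptive.

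Methods that handle incomplete times appear in two places, both about death. Data analysis states: "Kaplan-Meier estimates and log-rank statistics will be used for assessing cumulative risk of death at 12 months". Outcome measures, item (b), has "median time of survival assessed by the Kaplan-Meier estimator".

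Background shows that death before re-implantation is foreseeable, since "the overall case fatality rate in patients who underwent surgery in the RCT was still 29" per cent. The article gives no expected time to cranioplasty and no expected share of patients without one at a year.

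**The concern.** At the one-year contact an operated patient is in one of three states: re-implanted, dead without re-implantation, or alive and still waiting. Only the first has a time that can enter a mean, a median or a t test. Patients still waiting have the longest times, and those times are not yet known.

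The article uses time-to-event methods for survival but not for the other waiting time cut off by the same contact. Following the stated method would yield a figure that readers may take as the usual wait for cranioplasty, although it describes only those who reached it within the year. Comparisons between subgroups of operated patients could be distorted wherever mortality or the share still waiting differs.

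**Working it through.** **The plan's own figure.** There is none for cranioplasty. The only computed figure in the article, the Wilson interval for 0.76 with n = 300, reproduces (0.7086 to 0.8048, width 0.0963) and is not touched by this point.

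**Inputs.** From the article: follow-up of one year (365 days) and 29% case fatality in operated patients. Assumed, because the article is silent: log-normal time to cranioplasty T with median m of 90, 120 or 180 days and log-SD s of 0.5 or 0.8. Deaths total 29% by one year, either early (exponential, mean 20 days) or spread evenly over the year. Surgery and onset are treated as the same day.

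**Without deaths.** Let a = ln(365/m)/s.
- Share waiting at one year = 1 − Φ(a).
- Full (uncut) mean = m·exp(s²/2).
- Mean of observed times = uncut mean × Φ(a − s)/Φ(a).

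Largest case, m = 180, s = 0.8: a = 0.8837, so 1 − 0.8116 = 19% are waiting. The uncut mean is 180 × exp(0.32) = 247.9. The observed mean is 247.9 × 0.5333/0.8116 = 162.9, which is 34% short.

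Smallest case, m = 90, s = 0.5: a = 2.8002, so 0.3% are waiting. The uncut mean is 90 × exp(0.125) = 102.0. The observed mean is 102.0 × 0.9893/0.9974 = 101.2, which is 0.8% short.

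**With deaths.** A time is observed if T ≤ 365 and T precedes death, so the density of observed times is proportional to f(t)·S(t). Here S(t) = 1 − 0.29(1 − exp(−t/20)) for early deaths and 1 − 0.29t/365 for spread deaths. Numerical integration gives the following means in days (shortfall in brackets):

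| m, s | Uncut | No deaths | Early deaths | Spread deaths | Still waiting, with deaths |
|---|---|---|---|---|---|
| 90, 0.5 | 102 | 101 (0.8%) | 100 (1.5%) | 99 (3.1%) | 0.2% |
| 90, 0.8 | 124 | 107 (13.6%) | 105 (15.1%) | 102 (17.5%) | 2.8% |
| 120, 0.5 | 136 | 132 (3.0%) | 132 (3.3%) | 128 (5.6%) | 0.9% |
| 120, 0.8 | 165 | 130 (21.3%) | 129 (22.1%) | 124 (24.8%) | 5.8% |
| 180, 0.5 | 204 | 181 (11.0%) | 181 (11.1%) | 176 (13.5%) | 5.6% |
| 180, 0.8 | 248 | 163 (34.3%) | 162 (34.6%) | 156 (37.0%) | 13.4% |

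The median of observed times is 1% to 22% short over the scenarios with deaths (119 against 120 days, up to 141 against 180).

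**What drives the shortfall.** Early deaths add 0.1 to 1.5 percentage points to the shortfall in the mean, and spread deaths add 2.3 to 3.9. Most of the larger shortfalls come from patients still waiting.

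**What deaths change instead.** Take m = 120, s = 0.8. With early deaths, 66% are re-implanted by one year, 28% die first and 6% wait. With spread deaths the shares are 82%, 12% and 6%. The observed medians are close, at 109 and 105 days. The day by which half of all operated patients have been re-implanted is 178 in the first case and 128 in the second.

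**Group comparison.** Compare the last two rows under early deaths. The group with the longer uncut mean (248 against 204 days) has the shorter observed mean (162 against 181), because more of its long waits are unobserved. A t test on observed times would point the wrong way.

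**The case against.** The strongest reply is that an article condensing a fuller protocol need not state how one descriptive secondary outcome handles censoring, and that an analysis plan may do so. The list of statistics is introduced as inclusive and tied to the scale of the variable, so a time-to-event summary is not forbidden. This has weight, but the article does more than stay silent. It states a method for all outcomes, and choosing by scale leads a continuous time to mean, SD and median, because scale says nothing about incompleteness.

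Four stronger readings are tempting, and the article does not support them.

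- **The reported time is bound to be materially short.** That needs a material share still waiting at one year. The article gives no such share. With under 1% waiting, the shortfall in the table is 1% to 6%.
- **Death makes the time short.** Early death hardly moves the observed mean or median. What it changes is the population described.
- **The applicability qualifier removes waiting patients by design.** It may only mean patients who had a hemicraniectomy, since the same qualifier follows other treatment items. Under either reading, however, only re-implanted patients have a time to average. A conditional summary is legitimate if labelled as such.
- **The share reaching cranioplasty is lost.** Absolute and relative frequencies are planned and could supply it. With complete contact, the crude one-year proportion equals the cumulative incidence at one year.

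Two further points stand. Cumulative incidence does not estimate the uncut mean used as the benchmark above; it answers a different and better-defined question. And the harm is limited: conservatively treated patients have no cranioplasty, so the surgical-versus-conservative contrast is not affected, and the Discussion presents the registry as hypothesis-generating.

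**Conclusion.** The point holds in a limited form. Followed as written, the article summarises time to cranioplasty only among patients re-implanted by the one-year contact and does not say how the dead and the still-waiting enter. That summary tends to be too short. The shortfall in the mean is about 1% to 37%, and in the median about 1% to 22%, across the assumed log-normal timings with 29% mortality. These ranges rest on assumptions about timing that the article neither supplies nor contradicts, so they show sensitivity and do not predict what the registry will find. Death before cranioplasty mainly leaves the target population undefined and can distort comparisons between groups of operated patients. The point is minor: it concerns one descriptive secondary outcome and leaves the primary outcome and the sample size as they are.

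**What to change.** Add a sentence to Data analysis for outcome (f): in patients who had hemicraniectomy, estimate the cumulative incidence of cranioplasty from the date of hemicraniectomy to one year (Aalen–Johansen estimator), with death as a competing event and patients still waiting censored at last contact. Use a matching test, such as Gray's, for any group comparison. If a mean or median of observed times is also given, label it as conditional on cranioplasty within one year, and report beside it the numbers who died first and who were still waiting.

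The cost is slightly more analysis work, and a curve in place of a single mean. The cranioplasty and death times are already needed for the outcomes listed, and the method is standard in the planned SAS software.
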